| Project Justification / context | **RATIONAL FOR COVID-19:**  The current global SARS-Cov-2 viral pandemic, which is responsible for a new infectious disease called COVID-19, is a major health concern. The mortality of hospitalized patients with COVID-19 is 5% to 15% (MURTHY, JAMA, 2020). In 15% to 40% of cases, the disease is responsible for respiratory complications, and the most serious is acute respiratory distress syndrome (ARDS) (HUANG, LANCET 2020; ZHOU, LANCET 2020; WU, JAMA INTERN MED 2020).  The access to an intensive care unit (ICU) is about 15% to 30%, with mechanical ventilation use 10% to 25% from the first Chinese studies (HUANG, LANCET 2020; GUAN, N ENGL J MED 2020, GUO, LANCET CARDIOLOGY 2020, WANG, JAMA 2020). ARDS is present in two thirds of cases (WANG, JAMA 2020). Mortality of patients with ARDS is high (53%) (WU, JAMA INTERN MED 2020). In a smaller population of 21 Americans admitted to the ICU, 70% required invasive mechanical ventilation (ARENTZ, JAMA 2020).  The management of hospitalized COVID-19 cases is essentially symptomatic, with oxygen support in mild forms and invasive mechanical ventilation in the most severe forms. Drug studies are under way to find out how to avoid the worsening of respiratory symptoms.  The seriousness of this pandemic is related to the saturation of ICUs (GRASSELLI, JAMA 2020). Thus, trying to prevent worsening as much as possible could reduce the need for invasive or non-invasive mechanical ventilation.  **RATIONALE FOR PRONE POSITIONING FOR ARDS:**  ARDS is defined by the Berlin definition (ARDS DEFINITION TASK FORCE, JAMA, 2012) as diffuse lung injury occurring in patients with a predisposing risk factor.  Prone positioning (PP) has been shown to decrease mortality in patients with moderate to severe ARDS in the ICU.  In a study by Ding et al (DING, CRIT CARE, 2020), in non-intubated patients, the combination of PP (2 hr twice a day) and high flow oxygen therapy decreased the need for intubation in patients with moderate to severe ARDS.  We hypothesize that the use of PP in patients with spontaneous breathing (under conventional oxygen therapy) during acute respiratory distress caused by SARS-Cov-2 infection (COVID-19) would result in decreased incidence of intubation or non-invasive ventilation at 2 pressure levels or death as compared with usual care. |
| Primary Objective | To demonstrate that PP in spontaneously breathing patients decreases the risk of acquiring the following events, which can be seen as a composite endpoint:  - Endotracheal intubation  - Or non-invasive ventilation at 2 pressure levels  - Or death |
| Secondary objectives | To demonstrate that the use of PP improves (decreases) the World Health Organization (WHO) ordinal scale score by 2 points from randomization (CAO; N Engl J Med; 2020)  To demonstrate that PP in spontaneously breathing patients reduces the need for tracheal intubation and invasive mechanical ventilation.  To demonstrate that PP in spontaneously breathing patients reduces the use of non-invasive ventilation at 2 pressure levels.  To demonstrate that PP in spontaneously breathing patients reduces the time on oxygen therapy.  To demonstrate that PP reduces the length of hospital stay  To demonstrate that PP in spontaneously breathing patients decreases mortality at day 28 in COVID-19 patients.  To compare the in-hospital mortality of the 2 groups (PP and usual care)  To compare the incidence of the need for transfer to ICU between the 2 groups  To compare the incidence of the use of non-invasive ventilation and intubation between the 2 groups, over the entire hospital stay when the stay is longer than 28 days. |
| Primary Endpoint | The rate of treatment failure defined as a composite endpoint comprising intubation and/or non-invasive ventilation at 2 pressure levels and/or death, in each group. |
| Secondary Endpoints | The duration (in days) to improve (score decrease) the clinical WHO ordinal scale score from randomization to 28 days between the 2 groups  The rate of endotracheal intubation (%) for invasive mechanical ventilation at 28 days between the 2 groups  The rate of non-invasive ventilation at 2 pressure levels at 28 days between the 2 groups  The time on oxygen therapy from inclusion to day 28 between the 2 groups  The hospital length of stay between the 2 groups  The mortality at 28 days and during the hospital stay between the 2 groups  The rate of transfer to ICU at 28 days  The rate of use of non-invasive ventilation at 2 pressure levels and intubation over the entire hospital stay. |
| Study Method/ Design | This will be 2 parallel-group randomized controlled trial with 1:1 allocation ratio to usual care or intervention (PP).  The control group will be usual care in all participating departments/hospitals. The prone position will not be allowed during the day (allowed at night if it is the patient’s natural sleeping position).  The intervention group will undergo the following:   - Each day of hospitalization, at least 2 PP sessions during the day, with the objective to spend as much time as possible in PP if tolerated and a minimum of 2.5 hr cumulative time in PP during the day. - A session of PP as long as possible at night. Patients will be encouraged to sleep in PP as much as possible at night, knowing that monitoring the number of hours will not be feasible in COVID-19 medical wards in the current context.   Bedridden patients who are not able to self-position to the prone position or with minimal assistance of one person will not be included in the study.  Barriers will be positioned to avoid a potential fall out of bed.  The patient will be allowed to choose the best PP as long as the back of the thorax is not compressed by the bed. |
| Inclusion criteria | Patients > 18 and < 85 years old  Patients hospitalized with a laboratory-confirmed SARS-CoV-2 infection  Patients on oxygen therapy (nasal cannula, mask or high-flow nasal oxygen therapy)  Patients able to self-position to the prone position or with minimal assistance of one person  Signed the consent form  Patients hospitalized in a COVID-19 medical ward for < 72 hr |
| Non-inclusion criteria | Patients on oxygen therapy or continuous positive airway pressure or non-invasive ventilation at home  Patients with chronic obstructive pulmonary disease (COPD) (Gold stage 3 or 4)  Patients with known chronic diffuse interstitial lung disease  Patients with a chronic neuromuscular disease  Contraindication to PP (recent thoracic trauma, pneumothorax, unstable spine or pelvis fractures etc.)  Deep vein thrombosis or pulmonary embolism with curative anticoagulation for < 48 hr  Hemodynamic instability (mean arterial pressure < 65 mm Hg) persisting for > 1 hr  Respiratory rate > 40 cycles/min.  Excessive use of accessory respiratory muscles (as determined by the clinician)  Indication for curative non-invasive ventilation (acute pulmonary edema or acute hypercapnic respiratory failure)  Intestinal occlusive syndrome  Patients unable to protect upper airways  Patients discharged from intensive care after treatment with invasive or non-invasive ventilation for COVID-19  Inability to understand French or to follow instructions to perform awake PP.  Patients not affiliated with or excluded from the French social security system or under law protection (namely minors, pregnant or breastfeeding women, persons deprived of their liberty by court or administrative decision)  Do not intubate order |
| Strategy / procedures | - **Prone position plus usual care** - **Usual care alone** |
| Number of Patients | 268 |
| Duration of investigation | Inclusion period: Epidemic period of COVID-19  **Participation time for each patient.** The study intervention will stop when one of the following events is reached: initiation of non-invasive or invasive ventilation, death, or still hospitalized at day 28 without event. Patients hospitalized for > 28 days will continue to be followed in the study (rate of use of non-invasive or invasive ventilation, rate of admission to an ICU, death).  The duration of participation for each patient corresponds to the duration of the hospitalization (all wards combined) or longer in case of severe adverse events that would require longer follow-up. |
| Expected impacts | In the event that the PP would reduce the rate of non-invasive or invasive ventilation or death, it could be proposed as a standard-of-care technique for hypoxemic COVID-19 patients. |

List of acronyms

| AE  ARDS  CRA  CRF | adverse event  acute respiratory distress syndrome  clinical research assistant  case report form |
| --- | --- |
| COPD | chronic obstructive pulmonary disease |
| GCP | Good Clinical Practice |
| PP | prone position |

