## Statistical methods

A detailed analysis plan will be developed prior to the start of the study. The plan will be modified, if necessary, before the statistician is unblinded.

Oatient characteristics will be described by randomization group as number and percentages for categorical variables and mean (standard deviation) or median (25th and 75th percentile) for continuous variables, depending on their distribution.

The main analysis will be conducted on an intention-to-treat basis. However, data for patients withdrawing their consent during the study, in accordance with French law, will not be analyzed.

The primary endpoint (percentage of patients requiring intubation or non-invasive ventilation at 2 pressure levels, or who died within 28 days of inclusion) will be compared between the 2 groups (PP and usual care) by a Mantel-Haenszel 2-test stratified on the stratification variables #2 and #3 (SpO2 and BMI). The effect of the intervention will be expressed in terms of absolute risk difference and its 95% confidence interval (CI). The result of this analysis will be confirmed by a mixed-effect logistic regression analysis, with the recruiting center as the random effect and the study intervention and the stratification variables 2 and 3 as fixed effect variables. Interaction terms between the stratification variables and the intervention will be introduced into the model and retained only if they show a significant effect on the frequency of the outcome. Logistic regression analysis will be used to estimate the odds ratio and its 95% CI.

The binary secondary endpoints (intubation rate, rate of non-invasive ventilation at 2 pressure levels, rate of transfer to ICU, mortality) will be compared between the groups using the same method.

The time to clinical improvement (decrease of 2 points on the WHO scale) will be compared between groups by log rank test and presented as Kaplan-Meier curves. The difference in risk between the groups will be expressed as a hazard ratio (HR) and its 95% CI. This analysis will be secondarily adjusted for stratification variables, and possibly other covariables that would be misbalanced between groups, using a Cox proportional model provided the proportional assumption is verified.

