The durations (of oxygen therapy, non-invasive ventilation, hospitalization), will be compared between groups by Mann-Whitney U test adjusted for stratification variables [KAWAGUCHI; Statistics in Biopharmaceutical Research; 2011]. The difference in duration (of oxygen therapy, non-invasive ventilation, hospitalization) between groups will be expressed by its median and 95% CI obtained by bootstrapping (2000 unstratified samples).

We will conduct a per-protocol analysis including only patients of the intervention group who laid in a prone position for at least 2 hr each day, and patients of the usual care group who never laid in a prone position.

The above analyses will be repeated in prespecified subgroups formed according to the stratification variables #2 and #3 (SpO2 and BMI).

No interim analysis is planned.

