## Number of participants to be included in the research

With a rate of lost to follow-up of < 2%, a population of 268 patients would guarantee a power of at least 80% to demonstrate at the 2-sided alpha risk of 5%, a difference of 10% to 14% between the 2 groups concerning the composite primary endpoint (4% vs 14% or 10% vs 24%). The number of patients to be recruited is fixed at 268.

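### The synopsis words six secondary objectives as demonstrations while the body words them neutrally, and section 8.3 gives one P<0.05 without tying it to the primary endpoint

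*Protocol*

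**What the plan says.** The synopsis lists nine secondary objectives. Six are framed as something to demonstrate, as the primary is: a 2-point WHO-scale improvement, intubation, two-level non-invasive ventilation, time on oxygen, hospital stay and day-28 mortality. The last reads "To demonstrate that PP in spontaneously breathing patients decreases mortality at day 28 in COVID-19 patients". The other three (in-hospital mortality, ICU transfer, and ventilation over the whole stay) are framed as comparisons.

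In the body, under Objectives of the study, only the primary objective keeps the demonstration wording. The secondary objectives there are a neutral list of endpoints compared between the two groups.

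Section 8.1 gives the binary secondary endpoints the primary's stratified test: they "will be compared between the groups using the same method". Time to improvement gets a log-rank test and the durations a stratified Mann-Whitney test. It continues: "The above analyses will be repeated in prespecified subgroups formed according to the stratification variables #2 and #3 (SpO2 and BMI"). A per-protocol analysis is added, and no interim look is planned.

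Section 8.2 sizes the trial "to demonstrate at the 2-sided alpha risk of 5"% for the composite alone. Section 8.3 consists of one criterion, P<0.05, with no endpoint named. Section 8.1 also announces a detailed analysis plan, which is not at hand.

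**The concern.** The synopsis and the body disagree on the status of the secondary endpoints, and section 8.3 does not settle it. Taken together, the synopsis wording and the unqualified threshold allow the composite to be null while a reduction in mortality or intubation, or a result in one BMI or SpO2 subgroup, is reported as demonstrated because its own P value fell below 0.05.

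The 5% error rate is fixed for one test only, and the chance of a false finding somewhere among several tests is larger. A mortality or intubation claim would also carry more weight with readers than the composite, although the sample size was not set for either.

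**Working it through.** **1. The plan's own figure.** Inputs from section 8.2 are "4% vs 14% or 10% vs 24"%, two-sided 5%, 80% power, under 2% loss and 268 patients in total; the synopsis gives 1:1 allocation. With pooled variance,

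n per arm = [1.960·√(2p̄(1−p̄)) + 0.842·√(p₁(1−p₁)+p₂(1−p₂))]² / (p₁−p₂)²

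- 4% vs 14%: (1.960×0.4047 + 0.842×0.3985)²/0.10² = 127.4, so 128 per arm, 256 in total, and 256/0.98 gives 262. Power is 82.0% at 134 per arm and 81.1% at 131.
- 10% vs 24%: (1.960×0.5312 + 0.842×0.5219)²/0.14² = 111.8, so 112 per arm, 224 in total, and 224/0.98 gives 229. Power is 86.7% at 134 per arm and 85.9% at 131.

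The stated 268 with at least 80% power holds, for the composite. The protocol states no error rate for the secondary endpoints, so there is nothing further to reproduce.

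**2. Matching the six objectives to tests in section 8.1.** Intubation, non-invasive ventilation and mortality get the stratified Mantel-Haenszel test. WHO improvement gets the log-rank test. Oxygen time and hospital stay get the stratified Mann-Whitney test. Each of the six therefore has a test. The nine-objective list does not map as cleanly, because whole-stay ventilation is not named separately in section 8.1, so the main figures use six.

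**3. Chance of at least one P<0.05 among six overall tests, all six nulls true.** The correlation ρ between test statistics is an assumption; the documents give none. For independent tests:

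- either direction: 1 − 0.95⁶ = 26.5%
- false benefit of prone positioning only: 1 − 0.975⁶ = 14.1%

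For a common correlation ρ, with Φ and φ the standard normal distribution and density,

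either direction: 1 − ∫[Φ((1.96−√ρ·u)/√(1−ρ)) − Φ((−1.96−√ρ·u)/√(1−ρ))]⁶ φ(u) du

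The benefit-only version drops the second Φ term.

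| ρ | Either direction | False benefit only |
|---|---|---|
| 0 | 26.5% | 14.1% |
| 0.3 | 24.1% | 12.2% |
| 0.5 | 20.7% | 10.4% |
| 0.7 | 16.4% | 8.2% |
| 0.8 | 13.9% | 6.9% |
| 0.9 | 10.8% | 5.4% |
| one test | 5% | 2.5% |

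The six objectives name a direction, so the right-hand column measures a false demonstration. The middle column also counts false findings of harm.

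**4. Check with simulated patients.** The simulation had 134 per arm, three binary endpoints (assumed rates 12%, 8% and 5%) and three rank-tested endpoints, all driven by one latent severity, with no treatment effect. As the average correlation rose from about 0 to 0.49, the either-direction rate fell from 26.9% to 19.9% and the false-benefit rate from 14.3% to 9.9%. This agrees with the table.

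**5. Adding the subgroups.** These figures assume equal stratum sizes, which the protocol does not give. Six endpoints, overall and in the four one-way subgroups (SpO2 below or at least 95%, BMI below or at least 30):

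- either direction: 67% at ρ = 0, 56% at 0.5, 46% at 0.7
- false benefit only: 41%, 30% and 24%

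If the subgroups are instead the four crossed strata listed under Randomization, the either-direction range is 74% to 54% for ρ from 0 to 0.7.

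**The case against.** The strongest reply is that multiplicity rules and the labelling of secondary endpoints are commonly left to the analysis plan, which section 8.1 announces. That stands: the lack of a hierarchy or alpha split in this protocol is not a fault in itself. It does not dispose of the point, because the synopsis states demonstration objectives and section 8.3 states an unqualified threshold. An analysis plan that called these endpoints exploratory would contradict the synopsis.

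Second, the body already keeps the demonstration wording for the primary, and no sentence says outright that a secondary P<0.05 counts as demonstrated. Both are true. That is why the point concerns conflicting wording and an open-ended threshold, and not a declared rule for false claims.

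Third, section 8.1 plans interaction terms between the stratification variables and the intervention, so subgroups are not left to within-subgroup P values alone. This stands, although no subgroup claim is made conditional on an interaction.

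Three stronger readings are tempting but not supported:

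- **The primary claim is inflated.** It is not. There is one composite, one primary test and no interim analysis.
- **The 21% to 27% range is the risk of a false benefit claim, subgroups included.** It covers six overall tests only, counts both directions, and needs a correlation of 0.5 or less. Outcomes driven by the same respiratory course may correlate more strongly.
- **The expected-impacts statement licenses a standard-of-care proposal on one component.** The sentence, "PP would reduce the rate of non-invasive or invasive ventilation or death, it could be proposed as a standard-of-care technique", most naturally restates the composite, so nothing rests on it here.

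**Conclusion.** The point holds in limited form. The synopsis and body conflict on whether six secondary objectives are confirmatory, and section 8.3 leaves the reach of P<0.05 open. Together they let a secondary or subgroup result be presented as demonstrated beside a failed primary.

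The false-benefit risk over the six overall tests is two to almost six times the single-test 2.5% across correlations of 0.9 down to 0 (5.4%/2.5% = 2.2; 14.1%/2.5% = 5.6). This assumes that all six nulls are true and that the tests share a common correlation, which the documents do not give. The subgroups push the risk higher, by an amount that also depends on unstated stratum sizes. The sample size and the 5% error of the primary test are sound on this point. The correction should be made, but the trial's main conclusion does not depend on it.

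**What to change.** 1. In section 8.3, state that P<0.05 as a decision rule applies to the primary composite only.
2. In the synopsis, reword the six secondary objectives as comparisons, in line with the body.
3. In section 8.1, label secondary, per-protocol and subgroup results as supportive or exploratory, reported as estimates with 95% confidence intervals. Judge subgroup differences by the interaction terms already planned, not by a P<0.05 within one subgroup.
4. If the sponsor wants confirmatory secondary claims, name a short list in a fixed order. Test each at two-sided 5% only after a significant primary result, and stop at the first non-significant one. A Bonferroni split over all six is the alternative, at 0.05/6 = 0.0083 each. Either keeps the family-wise error over the tests it covers at or below 5%.

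The cost is a few sentences: no extra patients or data, and no change to the 268 or to the primary test. Section 8.1 allows the analysis plan to be modified before the statistician is unblinded, so it can be aligned at the same time. The price is that nominally significant secondary or subgroup results can no longer be presented as demonstrated.

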## Supervisory board

NA

# Context and scientific justification

## Pathology description and results of available clinical and non-clinical trials

### COVID-19

The current global SARS-Cov-2 viral pandemic, which is responsible for a new infectious disease called COVID-19, is a major health concern. The mortality of hospitalized patients with COVID-19 is 5% to 15% (MURTHY, JAMA, 2020). In 15% to 40% of cases, COVID-19 is responsible for respiratory complications, among which the most serious is acute respiratory distress syndrome (ARDS) (HUANG, LANCET 2020; ZHOU, LANCET 2020; WU, JAMA INTERN MED 2020).

The access to an intensive care unit (ICU) is about 15% to 30%, with mechanical ventilation use 10% to 25% from the first Chinese studies (HUANG, LANCET 2020; GUAN, N ENGL J MED 2020, GUO, LANCET CARDIOLOGY 2020, WANG, JAMA 2020). ARDS is present in two thirds of cases (WANG, JAMA 2020). The mortality of patients with ARDS is high (53%) (WU, JAMA INTERN MED 2020). In a smaller population of 21 Americans admitted to an ICU, 70% required invasive mechanical ventilation (ARENTZ, JAMA 2020).

The management of hospitalized COVID-19 cases is essentially symptomatic, with oxygen support in mild forms and invasive mechanical ventilation in the most severe forms. Drug studies are under way to find out how to avoid the worsening of respiratory symptoms.

The seriousness of this pandemic is related to the saturation of ICUs (GRASSELLI, JAMA 2020). Thus, trying to prevent worsening as much as possible could reduce the need for invasive or non-invasive mechanical ventilation.

### Acute respiratory distress syndrome (ARDS)

ARDS is a diffuse pulmonary inflammation. Various diseases can be responsible for ARDS, exhibiting acute generalized inflammation with significant cytokine discharge and diffuse damage to the vascular endothelium. ARDS is defined by the Berlin definition (ARDS DEFINITION TASK FORCE; JAMA; 2012) as diffuse lung injury occurring in patients with a predisposing risk factor. The criteria are as follows:

- Occurrence within 1 week of known insult or new or worsening respiratory symptoms

- Bilateral opacities not fully explained by effusions, lobar or lung collapse, or nodules on imaging

- Diagnosis of respiratory failure not fully explained by heart failure or fluid overload

- Presence of hypoxemia according to the PaO2/FiO2 ratio (P/F) with a positive end-expiratory pressure (PEEP) ≥ 5 cmH2O.

This last condition leads to classification into 3 ARDS subgroups:

o P/F 200 to 300: mild ARDS

o P/F 200 to 100: moderate ARDS

o P/F < 100: severe ARDS

Currently, excluding the SARS-CoV-2 epidemic, 5% of patients hospitalized with mechanical ventilation have ARDS criteria.

The main risk factors for ARDS are pneumonia, sepsis, inhalation of gastric fluid, chest trauma, pancreatitis and drowning.

Chest CT scan is an aid to diagnosis; it can detect healthy areas (properly ventilated) from unventilated areas (ground glass opacities or consolidation). Chest ultrasonography and the presence of B-lines can also identify areas affected by ARDS.

ARDS evolves in the following 3 phases that are theoretically successive but that can be mixed depending on mechanical ventilation and the occurrence of nosocomial infection (ALIAGA; Intensive Care Med; 2015):

1. Exudative or inflammatory phase

2. Proliferation phase (type II alveolar cells, fibroblasts and respiratory breakdown with increased risk of mortality)

3. Fibrotic phase (major increase in mortality risk, with a reduction in lung compliance)

The understanding of the physiology of ARDS has led to an improvement in ventilatory management. Ventilation must be "protective" (use of low insufflated volumes) and ensure adequate oxygenation with sufficient CO_2_ clearance. It allows for decreasing the extent of lung damage produced by the evolution of ARDS (ventilator-induced lung injuries).

Pharmacological and non-pharmacological strategies for the management of ARDS are outlined in the table below (UMBRELLO; Int J Mol Sci; 2016):

[figure not shown]

Prone positioning (PP) could reduce mortality in ARDS patients. PP results in a more homogeneous distribution of pulmonary stress and strain, thus protecting the lung against ventilator-induced lung injuries. It also improves oxygenation with an increase of the P/F ratio, an increase of pulmonary perfusion ventilation ratio, and a decrease of PaCO_2_ and improves the ventilation in dorsal regions. PP should be used in all patients under mechanical ventilation with severe ARDS for 16 consecutive hours to improve mortality and success of weaning from mechanical ventilation (GUERIN ; N Engl J Med ; 2013).

However, few studies have evaluated PP in spontaneously breathing patients.

